**4.3 Sample size calculation**

We have not identified any previous randomized studies investigating the use of cabergoline in patients with migraine. Here we conducted a pilot study. The sample size should be large enough to provide meaningful feedback and detect potential problems, and reflect the diversity and characteristics of the target population. A common rule of thumb is to use a sample size of at least 30 participants. Due to the short duration of the study, we expect a maximum dropout rate of 20%. We will therefore include 18 patients in each intervention group.

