**3. Methods**

**3.1.1 Design**

This trial is a prospective, randomized, double-blind, placebo-controlled pilot study testing the hypothesis that in patients with migraine, cabergoline 0,5 mg weekly will reduce number of monthly migraine days (MMD) more effectively than placebo. Participants will be randomized to treatment with cabergoline 0.5 mg once weekly or placebo in addition to any existing migraine treatment and followed up after three months (12 weeks) of intervention.

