**3.1.2 Randomization**

Thirty-six patients will be randomized to receive treatment with 0.5 mg Cabergoline or placebo once a week. The randomization is conducted in a 1:1 ratio in 2 blocks of 18 patients and performed by the Aarhus University Hospital Pharmacy. The corresponding order of numbering and treatment assignment is specified in a randomization list, which is kept at the Service Production Hospital Pharmacy throughout the entire process. The Hospital Pharmacy also labels both the investigational drug and the placebo. Along with the investigational drug, the Hospital Pharmacy provides sealed code envelopes (corresponding to the randomization) that can be broken for individual participants if it is necessary for the investigator to know the assigned treatment.

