**4.1 Statistical analysis**

Differences between study groups will be assessed with unpaired t-tests or using non-parametric statistics as appropriate. Ordinal variables will be assessed with chi-2 test for trend or Mann-Whitney U test and Pearson’s chi-square test or Fisher's exact test will be used to test differences between proportions. Two-sided statistical significance levels of 5% will be used and estimates will be presented with 95% confidence intervals.

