**4.2 Analysis population**

The results will be analyzed according to a modified intention-to-treat principle comprising all patients who undergo randomization and receive the study treatment. Patients who withdraw fter receiving the first study treatment will be censored at the date of withdrawal of consent. Patients who are lost to follow-up will be censored on the day of last study visit. Protocol violations will be monitored continuously. Data collected during the study will be coded so that no subjects can be identified.

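### At the protocol's own maximum dropout of 20%, 36 randomized patients leave about 29, one short of the minimum of 30 from which the size is derived (minor)

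*Protocol*

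**What the plan says.** Section 4.3 of the protocol gives no power calculation. It reports that no earlier randomized study of cabergoline in migraine was found, calls the trial a pilot, and sets the size in three steps:

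- The starting point: "A common rule of thumb is to use a sample size of at least 30 participants".
- The allowance: "Due to the short duration of the study, we expect a maximum dropout rate of 20" per cent.
- The conclusion: "We will therefore include 18 patients in each intervention group".

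The total of 36 is repeated in the synopsis, in Section 3.2 and in Section 3.1.2 ("Thirty-six patients will be randomized to receive treatment with 0.5 mg Cabergoline or placebo once a week"). Section 3.1.2 also fixes the allocation: "The randomization is conducted in a 1:1 ratio in 2 blocks of 18 patients". Section 4.2 defines the analysis set by a "modified intention-to-treat principle comprising all patients who undergo randomization and receive the study treatment".

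**The concern.** The conclusion in Section 4.3 is introduced as following from the two statements before it. The natural reading is that 36 is the minimum of 30 enlarged so that 30 remain after dropout. An allowance for a maximum dropout should still hold when that maximum occurs, and this one does not.

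What is at stake is modest. Section 4.3 is the only justification of the trial's size, and its one implicit calculation does not give what it is meant to give. If dropout came close to the stated limit, the trial would miss its own minimum while running within its own assumptions.

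**Working it through.** **Inputs, all from the protocol**

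- Minimum size: 30 in total (Section 4.3)
- Maximum dropout: d = 20% (Section 4.3)
- Randomized: 18 per group, 36 in total (Sections 4.3 and 3.1.2)
- Allocation: 1:1 (Section 3.1.2)
- Confidence intervals: 95% (Section 4.1)

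**Step 1: reproduce the stated figure.** Section 4.3 shows no formula. Multiplying the minimum by (1 + d) gives 30 x 1.20 = 36, or 15 x 1.20 = 18 per group, which matches exactly. That this was the route taken is an inference from the match.

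**Step 2: what remains at the stated maximum.** 36 x (1 - 0.20) = 28.8. In whole patients:

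| Dropouts | Share of 36 | Remaining | Within 20%? |
|---|---|---|---|
| 6 | 16.7% | 30 | yes |
| 7 | 19.4% | 29 | yes |
| 8 | 22.2% | 28 | no |

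The worst case allowed by the protocol's own limit is therefore 29, one below 30.

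**Step 3: the dropout rate that 36 can absorb.** 1 - 30/36 = 16.7%, or 6 patients.

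**Step 4: the size that covers a full 20%.** The allowance has to divide by the retained fraction: 30 / (1 - 0.20) = 37.5, rounded up to 38 (19 per group). Check: 38 x 0.80 = 30.4.

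**Step 5: what the missing patient costs in precision.** For a difference in means between two groups, the half-width of the 95% confidence interval in SD units is t(0.975; n1 + n2 - 2) x sqrt(1/n1 + 1/n2).

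- 30 patients, 15 per group: t(28) x sqrt(2/15) = 2.048 x 0.365 = 0.75 SD
- 29 patients, 14 and 15: t(27) x sqrt(1/14 + 1/15) = 2.052 x 0.372 = 0.76 SD

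The difference is about 0.01 to 0.02 SD. The result stays in SD units because the protocol gives no SD for the change in monthly migraine days.

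**The case against.** Four arguments speak for leaving the text alone.

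- **Thirty need not mean completers.** Section 4.3 speaks only of the sample size, and 36 randomized patients satisfy a minimum of 30 literally. This stands as a limit on certainty. But if 30 meant patients randomized, the dropout statement would have no function, and nothing in the section would explain why 36 was chosen.
- **Twenty per cent is a ceiling.** Correct. No expected dropout rate is stated, so 28.8 must not be reported as the expected number of completers; any dropout up to 16.7% meets the minimum. The point concerns only the range between 16.7% and 20%, which the protocol allows for.
- **The modified intention-to-treat set keeps treated patients who drop out.** Also correct, so dropouts do not automatically leave the analysis population. However, the primary endpoint in Section 3.3.1 needs diary data from the final 28 days of treatment, and Section 4.2 censors patients who leave. Some dropouts may therefore not contribute to the primary comparison.
- **One patient is trivial in a pilot.** In precision, yes. That limits the severity but does not make the derivation right.

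A reader might also infer that the trial is underpowered, because Section 3.1.1 frames it as a test of an efficacy hypothesis and Section 4.1 says "Two-sided statistical significance levels of 5% will be used", and that a non-significant result would be taken as no effect. The documents do not support making that part of this point. The protocol calls the trial a pilot, openly uses a rule of thumb and claims no power, so no power statement is wrong. It has no rule that treats a non-significant result as absence of effect, and Section 4.1 already commits to reporting estimates with 95% confidence intervals.

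**Conclusion.** The point holds as a minor one. If 30 is the number meant to remain after dropout, 36 randomized patients fall one short at the stated maximum: 29 in whole patients, with 28.8 as the arithmetic value. The minimum is kept up to 16.7% dropout and missed between there and 20%. The loss of precision is about 0.01 to 0.02 SD in the confidence interval half-width.

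Two stronger readings go too far. A reader might infer that a size of 36 and a dropout limit of 20% contradict each other. They do not; the conflict arises only with the third premise, that 30 must remain. A reader might also round 14.4 per group down to 14 and judge the trial on that number. But 14 per group is 28 patients, which means 22.2% dropout, outside the limit the protocol sets.

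The conclusion rests on one assumption, the after-dropout reading of 30. It needs no assumption about the SD or the treatment effect.

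**What to change.** Keep 36 and correct the statement in Section 4.3, for example: *With 36 randomized, at least 30 patients will complete if dropout is at most 16.7% (6 of 36); at the maximum dropout of 20%, about 29 would remain.*

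This costs one sentence and makes the stated figure slightly less favourable. It needs no extra patients and leaves the two blocks of 18 in Section 3.1.2 as they are.

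Raising the total to 38 would also repair the arithmetic. It would mean changing the number in the synopsis and in Sections 3.1.2, 3.2 and 4.3, and revising the block structure. That is more than a one-patient shortfall warrants.
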